#### Estimation of costs

Cost estimation will include all expenditures and resources associated with the alternative interventions during the 1-year follow-up period. Relevant costs will be grouped into dental costs (items used for treatment) and nondental costs (e.g., transportation fares). Some assumptions were made for the inclusion and valuing of relevant resource items: (1) no capital costs will be considered, (2) societal costs related to broader costs to society (e.g., productivity losses resulting from treatment, family costs, dietary adaptation, etc.) will not be included.

Cost estimation will involve three stages: identification of relevant resource items used for treatment associated with the provision of the interventions; estimation of the amount of resources used (in natural units); and application of prices (unit costs) to each of the resource items. Table 2 details the parameters that will be used in cost analysis, according to the treatment groups.

**Table 2 Tab2:** Description of items included in cost analysis, quantification, sources and references for item valuing for the two alternative treatments

Resource items	Cost calculation	Cost estimation method	Source for resource valuing	Estimated for treatment groups	
				CD	SIMO
Dental direct costs					
Overall clinical time					
Denture fabrication	(Monthly wage/monthly working time) × time spent	Time in min	Reference salary	Yes	Yes
Implant surgery time	(Monthly wage/monthly working time) × time spent	Time in min	Reference salary	No	Yes
Overdenture time	(Monthly wage/monthly working time) × time spent	Time in min	Reference salary	No	Yes
Follow-up	(Monthly wage/monthly working time) × time spent	Time in min	Reference salary	Yes	Yes
Implant	Units × price per unit	Microcosting	Price catalog	No	Yes
Prosthodontic components	Units × price per unit	Microcosting	Price catalog	No	Yes
Medication	Units × price per unit	Microcosting	Reference price	No	Yes
Imaging exams	Units × price per unit	Gross-costing	Mean market prices	Yes	Yes
Surgical consumables	Overall consumable resources/cases	Microcosting	Mean market prices	No	Yes
Prosthodontic laboratory	Units × price per unit	Gross-costing	Reference prices	Yes	Yes
Blood tests	Overall cost of exams per patient	Gross-costing	Reference prices	No	Yes
Consumables					
Infection control and PPE	Overall consumable resources/cases	Microcosting	Mean market prices	Yes	Yes
Dental materials	Overall consumable resources/cases	Microcosting	Mean market prices	Yes	Yes
Instruments/equipments					
Conventional denture	Estimation of lifespan for each item	Estimated annual costs	Panel of specialists	Yes	Yes
Implant/overdenture	Estimation of lifespan for each item	Estimated annual costs	Panel of specialists	No	Yes
Nondental direct costs					
Transportation fares	Number of visits per patient	Self-reported	Cost from public transportation	Yes	Yes

*CD* conventional mandibular denture, *PPE* personal protective equipment, *SIMO* single-implant mandibular overdenture

Overall costs for the two alternative treatments will include the summative value of all direct costs listed in Table 2. The currency used for cost estimations will be Brazilian reals – BRL R$. Price date will be recorded and values will be adjusted to the year of the registered costs by applying specific price indexes. If currency conversion is required for the final report, purchasing power parity (PPP) will be used to equalize the purchasing power of different currencies by eliminating the differences in price levels between countries. Alternatively, a widely used currency, such as the US dollar, will be adopted for cost estimations.

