### Economic analysis

#### Study perspective

A cost-effectiveness analysis will be performed from the health care provider perspective. Cost estimations of the study interventions will be derived from the clinical trial, which is a reproduction of a typical private setting for oral health care in Brazil, since implant treatment is not covered by the public health system and has limited reimbursement from insurance companies. An additional analysis will be performed using the patient perspective, in which costs will be estimated according to the reference pricing of dental procedures and treatments by the Brazilian Dental Association (Classificação Brasileira Hierarquizada de Procedimentos Odontológicos – CBHPO) and reference gross costs will be derived from a panel of specialists.

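### The cost rules conflict: transport fares are summed into a provider-perspective total, and equipment annualised over its lifespan is costed although capital costs are excluded, so the incremental cost is not uniquely defined

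*Protocol article*

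**What the plan says.** Study perspective sets the viewpoint: "A cost-effectiveness analysis will be performed from the health care provider perspective". It then adds a second one: "An additional analysis will be performed using the patient perspective". The second analysis is to be valued from a national reference list of dental procedure prices and from gross costs supplied by a specialist panel. Travel is not mentioned there.

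Estimation of costs sorts costs into dental and nondental groups, gives transport fares as the example of the nondental group, and lists two exclusions. One is broader societal costs. The other is that "no capital costs will be considered".

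Table 2, in the same section, includes these rows:

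- Under dental direct costs, a block headed "Instruments/equipments", calculated by "Estimation of lifespan for each item" and valued as "Estimated annual costs". Its conventional-denture row applies to both arms. Its implant/overdenture row applies to SIMO only.
- Under nondental direct costs, transport fares for both arms, counted by visits per patient, self-reported, and priced at public-transport cost.

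The text below the table gives the aggregation rule: "Overall costs for the two alternative treatments will include the summative value of all direct costs listed in Table 2". No row is assigned to a perspective.

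**The concern.** The incremental cost is the numerator of every incremental cost-effectiveness ratio (ICER) in the trial, and the study hypothesis is that this increment is relatively low for the benefit gained. Two features of the cost rules bear on that numerator.

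First, a provider-perspective total should hold costs that fall on the provider. Fares counted per patient visit and reported by the patient look like a cost to someone else, yet the aggregation rule puts them in the overall cost.

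Second, spreading the cost of a durable item over its lifespan to obtain an annual amount is the usual way of costing capital. One sentence excludes capital; the table and the aggregation rule include it.

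Neither item can be assumed to cancel between arms. One equipment row is SIMO-only, and SIMO has extra scheduled visits. Both push the SIMO-minus-control cost upward if included, apart from any offset through unscheduled visits. If the choice is left open until costs are known, it can be made with the result in view.

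**Working it through.** The article states no unit cost, fare, equipment price, lifespan or expected incremental cost, so there is no figure to reproduce. The check sets the rules side by side and works out what each does to the increment.

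**Set-up.** Write the incremental cost per patient as

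ΔC = D + A + F × (V_SIMO − V_CD)

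- D: difference in all other Table 2 items
- A: annualised implant/overdenture equipment cost per patient (SIMO only)
- F: return fare per visit
- V: visits per patient in each arm

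The conventional-denture equipment row applies to both arms, and the denture steps are the same in both. It changes each arm's total but largely cancels in ΔC.

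**Fares.** Scheduled SIMO-only contacts, from Surgical and prosthodontic procedures:

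1. implant surgery
2. suture removal at 7 days
3. abutment and matrix connection at 3 weeks

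So V_SIMO − V_CD = 3 + u. Here u is the net difference from all other visits, and the fare term is (3 + u)F.

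- With other visits equal, u = 0 and the term is 3F.
- Separate trips for presurgical imaging, for blood tests, and for a t1 visit distinct from the 3-week contact (Table 1 marks t1 for SIMO only) would give u = 3 and 6F. The article does not say that any of these needs its own trip.
- If control participants need more unscheduled adjustment or repair visits, u falls. Three more per patient would give u = −3 and a term of zero.

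Under a total limited to provider-borne costs, with fares not paid by the provider, the fare term should be absent. Under the aggregation rule as written, it is present.

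**Equipment.**

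| Statement followed | Equipment in ΔC |
|---|---|
| Capital exclusion, read to cover lifespan-costed equipment | 0 |
| Table 2 and the sum over all its rows | A |

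The two differ by A, the whole SIMO-only row.

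**Effect on the ICER.** Dividing by the effect difference carries these amounts through. As an illustration, take the 7.4 OHIP-EDENT units assumed in Sample size estimation as the size of the effect. The fare term then adds 3F / 7.4 ≈ 0.41F per unit, and the equipment choice moves the ratio by A / 7.4 ≈ 0.14A per unit. Without F and A, no currency value follows.

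**Coverage by sensitivity analysis.** Cost-effectiveness analysis gives implant/component costs and time horizon as examples of parameters to vary. The list is open-ended, but it names neither equipment nor travel.

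**The case against.** *The total is determinate.* Capital costs is an undefined term. Table 2 gives equipment its own method, source and arm allocation, and the aggregation rule says to sum the table. If the specific table governs and capital means only premises or fixed installations, the passages agree and no number changes. This stands in part. A reader might infer that the incremental cost is wrong because equipment is included; the article does not support that. But it does not state the reconciling definition either, so two totals remain open.

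*The payer of the fares is not stated.* This is correct. The article says only that participants are not charged for treatment. That patients bear the fares is a strong inference from the nondental label, the self-report and the public-transport price, but it is not a stated fact. The point survives because nothing says the provider pays.

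*The patient analysis may include fares.* One might read it as using only reference treatment prices. That goes too far, since panel-derived gross costs are also named. What can be said is that its description does not mention fares.

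*The extra visits are uncertain.* A lower bound of four is tempting if imaging and blood tests are counted as a visit, but the article does not require a separate trip for them. Three scheduled contacts are firm; the net difference also depends on unscheduled visits.

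*An article may leave item-by-perspective detail to the full plan.* That would answer a gap. Here the article gives an explicit summing rule that does not fit its stated perspective.

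**Conclusion.** Both conflicts are in the current text, and they differ in kind.

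- **Fares:** following the stated rule puts a cost not shown to be the provider's into the provider total. The amount is about 3F or more in the increment, assuming otherwise equal visits and fares not paid by the provider. The net amount depends on unscheduled visits and on F, and may be small beside implant and component costs.
- **Equipment:** the increment is ambiguous by A. It is not shown to be wrong.

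No effect on the trial's conclusion is demonstrated, because the article gives no prices. The point should still be settled before costs are analysed, since it concerns the numerator of the trial's main result and costs almost nothing to resolve.

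**What to change.** 1. Restrict the provider-perspective total to provider-borne (dental direct) costs, and move transport fares to the patient-perspective total. A column in Table 2 marking each row by perspective would do this. The sentence below the table should then refer to the rows marked for the perspective in question.
2. Define capital costs so that the lifespan-annualised instruments and equipment in Table 2 are explicitly kept, for example by excluding only premises and fixed installations.
3. Report the ICER without the equipment rows as a sensitivity analysis.

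The cost is minor rewording and one extra re-summing of items already collected. No new data, visits or participants are needed.

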### Data analysis

#### Descriptive and inferential statistics

Data will be checked and cleaned blind to the treatment group allocation and analysis will be carried out according to the intention-to-treat principle. Statistical analysis will comprise between-group comparisons of the effectiveness outcomes (OHIP and patient satisfaction) and will be performed using independent *t* tests or nonparametric tests in case of asymmetric distribution of data (IBM-SPSS 23.0 software; IBM Corp, 2015). An alpha level of 0.05 will be set for significance.

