### Sample size estimation

In this study, sample size was estimated for each of the two treatment groups considering a minimum power of 0.80 (type II error rate) at a two-sided 0.05 significance level (type I error rate). A previous single-group clinical trial that assessed the incremental effect of the SIMO treatment compared to the CD, and considered the outcome satisfaction with the dentures and OHRQoL, served as the data source for this sample size estimation [23]. A minimum of 24 patients will enter this two-treatment parallel-design study, considering that the true difference between treatments is 7.4 units for OHIP-EDENT and 2.6 units for satisfaction scores, assuming unequal variances for both groups. An increase of 10 % to reduce the impact of loss to follow-up on study power resulted in a minimum final sample of 28 participants, 14 in each treatment group.

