### Randomization

A computer-based random number generator will be used to assign participants into the treatment groups [24]. In order to prevent imbalance between groups, participants will be stratified according to gender [25]. Block randomization will be used to randomly assign participants to sets of different sizes, using unsorted numbers with a range from 1 to 2 (representing the two treatments) and an allocation ratio of 1:1 for the control and experimental groups. The sequence will be concealed in opaque, consecutively numbered envelopes for each block. After each enrollment, the next randomization envelope will be opened, according to the previously established sequence. An independent collaborator will manage the allocation and inform participants about their assigned groups.

If a participant allocated to the SIMO group refuses to receive the implant treatment (noncompliance), follow-up will occur the same way as in the control group. Moreover, intention-to-treat analysis will be performed, which means that during statistical analysis noncompliant participants will be kept in their original group, even if they did not receive the allocated treatment. This may provide a more conservative estimation of treatment effect, minimizing the probability of type I error occurrence [26].

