### Masking/blinding

To avoid selection bias and ensure adequate allocation concealment, their treatment group will only be revealed for each participant after the assessment of the baseline outcomes, which will occur after the delivery and regular use of the new set of conventional dentures. Since full blinding for the two interventions is not possible for those involved with treatment management and collection of data, only those collecting and analyzing clinical data from masticatory performance tests will be unaware of the assigned treatment.

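### Both primary outcomes are tested without adjusting for baseline score or gender, possibly by a rank test, which costs precision and can separate the p value from the ICER

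*Protocol article*

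**What the plan says.** The section Descriptive and inferential statistics tests OHIP-EDENT and satisfaction between arms with independent t tests, or with "nonparametric tests in case of asymmetric distribution of data". It names no covariate and no criterion for asymmetry. It does not say whether follow-up scores or changes from baseline are compared.

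Other sections bear on this choice:

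- Masking/blinding: the arm is revealed only "after the assessment of the baseline outcomes, which will occur after the delivery and regular use of the new set of conventional dentures". Table 1 marks both primary outcomes at baseline, 6 and 12 months. It places the baseline column after allocation, but the text is clear that participants do not know their arm when they answer.
- Randomization: "participants will be stratified according to gender", in blocks, 1:1.
- Outcomes: gender and baseline clinical variables are kept for describing patients and for subgroup analysis. Adjustment is not mentioned.
- Cost-effectiveness analysis: the ICER divides the cost difference by the difference in effectiveness between arms, with satisfaction and OHRQoL as the effectiveness measures.
- Sample size estimation: 24 patients, raised to 28 (14 per arm), assuming that "the true difference between treatments is 7.4 units for OHIP-EDENT and 2.6 units for satisfaction scores".

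**The concern.** Each participant supplies a score on the outcome itself while wearing new conventional dentures and not yet knowing the arm. That is usually a useful covariate, and here it costs no extra visit. The stated test does not name it, nor the factor that randomization was built on. In a trial of 28, a plain comparison of follow-up scores then carries avoidable noise, and part of any chance baseline difference stays in the estimate and hence in the ICER denominator.

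The second strand is the choice between tests. If the data look skewed, the p value comes from ranks, while the ICER still needs a difference in score units. The trial exists to estimate cost-effectiveness, so its effectiveness test and its ICER should describe the same quantity.

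**Working it through.** **Inputs from Sample size estimation.** Difference 7.4 OHIP-EDENT points; power 0.80, two-sided 0.05; 24 patients (12 per arm), inflated to 28 (14 per arm).

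**Assumptions.** No SD is stated, only "assuming unequal variances for both groups", and no baseline-to-follow-up correlation (ρ). I assume equal variances, the same SD at baseline, that 7.4 points is the difference that sets N, that follow-up scores are compared, and ρ from 0 to 0.7.

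**Step 1: the plan's own figure.** The inflation reproduces: 12/0.9 = 13.3 and 12 × 1.1 = 13.2, both rounding up to 14 per arm, 28 in total. The base of 24 cannot be reproduced without an SD. Back-solving the noncentral t (12 per arm, 22 df, power 0.80) gives a standardized difference of 1.197, so SD = 7.4/1.197 = 6.18. The normal approximation gives 1.144 and 6.47.

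**Step 2: precision.** ANCOVA multiplies the error variance by 1 − ρ². Its noncentrality at 12 per arm is 1.197 × √6 / √(1 − ρ²), on 24 − 4 = 20 df. A t test on change scores has variance factor 2(1 − ρ). The simulation used 8,000 trials per setting, with baseline and gender as covariates.

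| ρ | 1 − ρ² | SE ratio | ANCOVA power, formula | ANCOVA power, simulated | Unadjusted N for equal precision, 24/(1 − ρ²) | Change-score power |
|---|---|---|---|---|---|---|
| 0 | 1.00 | 1.000 | 80% | 78% | 24 | 51% |
| 0.3 | 0.91 | 0.954 | 83% | 82% | 26 | 66% |
| 0.5 | 0.75 | 0.866 | 90% | 88% | 32 | 80% |
| 0.7 | 0.51 | 0.714 | 97% | 97% | 47 | 95% |

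The unadjusted comparison has 80% throughout (80.5% in the simulation at ρ = 0). Simulated type I error for ANCOVA was 4.6–5.6%.

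**Step 3: chance imbalance at 14 per arm.** The SE of the baseline difference is 6.18 × √(2/14) = 2.34 points. The probability that it exceeds 2 points in either direction is 2 × [1 − Φ(2/2.34)] = 0.39. Only ρ times the imbalance reaches a follow-up comparison:

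- ρ = 0.3: 0.6 points, 0.6/7.4 = 8%
- ρ = 0.5: 1.0 points, 1.0/7.4 = 14%
- ρ = 0.7: 1.4 points, 1.4/7.4 = 19%

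If the difference would otherwise be 7.4 and the incremental cost is fixed, the ICER is multiplied by 7.4/6.8 = 1.09 to 7.4/6.0 = 1.23 when the imbalance shrinks the denominator, and by 7.4/8.0 = 0.93 to 7.4/8.8 = 0.84 when it enlarges it. Change scores shift the opposite way, by (ρ − 1) × 2 = −1.4, −1.0 and −0.6 points.

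**Step 4: ignoring the stratum.** With gender balanced within arms and ρ = 0.5, the unadjusted t test had simulated type I error 4.4% if gender shifts the outcome by 0.5 SD and 2.8% at 1 SD. ANCOVA with gender gave 5.1% and 5.3%.

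**Step 5: switching tests.** Choosing by a Shapiro-Wilk check in each arm at 14 per arm left type I error at 5.4% (normal data) and 5.1% (lognormal). The t and rank tests disagreed in 2–3% of null trials.

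**The case against.** The strongest reply is that nothing here is invalid. Randomization makes the unadjusted t test unbiased, and its standard error already allows for chance imbalance. Ignoring gender errs on the conservative side, and choosing between tests barely moves the type I error. All of that stands.

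The size is also uncertain. The SD is back-solved under equal variances although the plan assumes unequal ones, and using it at baseline is a further assumption. Sample size estimation draws on a single-group study, so the SD behind the 24 could even be that of a within-person change. The correlation is unknown, and at zero ANCOVA loses a little. If change scores are meant, baseline is already used, although that gains power only when the correlation exceeds 0.5 and leaves an imbalance effect of opposite sign. These points limit the numbers. They do not favour the stated method.

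A rank test does not leave the ICER without a denominator: the Cost-effectiveness analysis section computes it from the arms' effectiveness, whichever test supplies the p value. What stands is narrower: the test and the ICER may then address different quantities.

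Finally, one may say that covariates belong in a fuller analysis plan. That would answer a silent article, but this one names its test and gives the baseline variables another use.

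**Conclusion.** The point holds as a matter of efficiency and coherence. The plan fixes an unadjusted comparison although a baseline score taken before the arm is revealed and a stratification factor are at hand. Under the stated assumptions, adjustment is worth about 2 to 17 points of power for correlations of 0.3 to 0.7 and costs about 2 points at zero. A 2-point imbalance left unadjusted moves the follow-up difference by 8–19% of the planned effect. None of these sizes can be fixed from the protocol, which gives neither the SD nor the correlation.

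A reader might infer three stronger things that the documents do not support: that the t test is biased or inflates type I error; that the whole baseline imbalance enters the result; or that the data-driven choice of test is itself a serious threat to the error rate. The change should be made, but the trial is not invalid without it.

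**What to change.** For each primary outcome, prespecify ANCOVA of the 12-month score on arm, baseline score and gender, reported as an adjusted mean difference with 95% CI. If residuals are skewed, keep the model and replace the normal-theory inference with a bootstrap CI or a permutation p value, rather than moving to a rank test. Use the same adjusted mean difference as the ICER denominator. State that the modelled outcome is the 12-month score and not the change, which removes the present ambiguity.

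The cost is a change of wording, two degrees of freedom, and about 2 points of power if baseline proves uninformative. No extra patients, visits or data are needed. The choice should be fixed before outcome data are seen.
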